#### Follow-up period and outcomes

The primary outcome is all-cause mortality 3 years from the start of treatment (time zero). We will also report all-cause and lung-cancer specific mortality at 3 months, 6 months, 12 months, 24 months and 36 months as secondary outcomes. We will define lung-cancer attributable mortality as those deaths which include lung cancer (International Classification of Diseases-10: C34) as a cause of death. Multivariable flexible hazard models^54^,^56^ will be fitted to estimate the effect of SABR versus surgical resection on time to death for both all-cause and lung-cancer specific mortality. For these time-to-death analyses, individuals treated during 2015–2023 inclusive will be included to maximise follow-up duration.

The number of days in hospital in the 12 months after the start of treatment will be recorded. We will use information on reasons and route of admission (eg, via emergency room) in the 90 days following the start of treatment to identify admissions attributable to grade three or four adverse events following either treatment modality (see also CEA).

In the pilot NDRS linked registry data, information was available for the primary endpoint (3-year mortality) for each individual in the eligible population. Covariate information was also complete for all the required covariates for the eligible population with the exception of ethnicity, for which the proportions with missing data were low and similar between the comparison groups (1.71% for SABR and 1.34% for surgical resection). The analysis will therefore use observations with complete case information which assumes the missing ethnicity data are independent of the outcome given the covariates included in the analytical models.^57^

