### Data

An overview of the datasets and their purpose is presented in table 1. We will use England’s NDRS Cancer Registry data to identify individuals aged 18 and over diagnosed with early-stage (T1-2N0M0) NSCLC in 2015–2020 inclusive. The Cancer Registry collects comprehensive data on all malignant tumours diagnosed in England recorded by NHS healthcare providers as part of routine care. These data include information on tumour and patient characteristics, geographical location, vital status (alive, deceased, emigrated or lost to follow-up), and for this study, it will use follow-up data until the end date of 31 December 2023.

**Table 1 T1:** Overview of the different datasets within the ‘NDRS linked data’ and their proposed use in the SORT target trial for NSCLC

Dataset	Purpose in the study
National Disease Registration Service (NDRS) Cancer Registry	Identify individuals diagnosed with T1-2N0M0 NSCLC between 2015 and 2020 (base case) and between 2015 and 2023 (alternative analyses) Obtain vital status Collect patient and tumour characteristics (e.g., age at diagnosis, income deprivation, sex, tumour stage, histology)
Hospital Episodes Statistics inpatient and outpatient	Identify individuals who underwent surgical resection within 6 months of diagnosis Collate resource use (e.g., hospitalisations, outpatient visits, surgical procedures) Collect measured confounders (e.g., comorbidities and frailty) Define time zero (date of curative surgery)
Radiotherapy Data Set	Identify individuals who received SABR within 6 months of diagnosis (base case) Collate use of different radiotherapy regimens Identify time zero (date of first dose or radiotherapy)
Systemic anti-cancer therapy	Collate use of different immuno-oncology and chemotherapy regimens including those with palliative intent
Cancer outcomes and services data set	Obtain Zubrod performance status

M, Metastases; N, node; NSCLC, non-small cell lung cancer; T, tumour.

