#### Covariates and time zero

The target trial approach requires baseline covariates to reduce the risk of confounding and to undertake subgroup analyses. From the NDRS Cancer Registry, we will obtain demographic and tumour data including: age at diagnosis, sex, year of diagnosis, tumour histology (adenocarcinoma, squamous, other), tumour stage (T1N0M0, T2N0M0), ethnicity (white, black, South-Asian, other, missing) and income quintile of the Index of Multiple Deprivation.^52^ Zubrod performance status^51^ will be obtained from the Cancer Outcomes and Services Data. From the HES data, we will define comorbidities from inpatient and outpatient visits that include the following diagnoses in the 5 years before the NSCLC diagnosis: myocardial infarction, stroke, heart failure, chronic obstructive pulmonary disease, peripheral vascular disease, diabetes, and interstitial lung disease.

We will define ‘time zero’, which is analogous to the time of randomisation as it is when eligibility criteria are met and follow-up starts, to be the first date that SABR with curative intent is received or surgical resection is undertaken. We will define covariates for ‘seasonality’ by the month either treatment modality was first received, and ‘treatment waiting time’ as the time between the decision to treat and ‘time zero’. We will capture quality of care measures including waiting times and the volume of surgical resections performed in the 12 months before time zero. We will define the cancer alliance and the NHS region within which the surgical hub is located, to account for regional variations.

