#### Resource use and unit costs

From the linked NDRS data, we will identify resource use for those categories anticipated to drive incremental costs, including the delivery of SABR, surgical procedures, hospital inpatient stays (including all readmissions, subsequent surgery, palliative care), outpatient visits, diagnostic procedures and subsequent treatment (eg, systemic therapies, radiotherapy or salvage surgeries). We will extract data on the receipt of SABR as well as the Office of Population Censuses and Surveys Classification of Interventions and Procedures codes of all surgical resections and operative procedures performed on each eligible patient. For hospital inpatient stays, we will distinguish between the time spent in critical care and on general wards.

Unit costs, including those for SABR and surgical strategies, will be taken from the NHS Cost Collection^63^ and the Personal Social Services Research Unit Cost databases.^64^ We will combine resource use with unit costs to report total costs per patient over 3 years (see also the Alternative analyses section).

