**Figure 3 F3:**
[figure not shown]
Balance of baseline covariates across different levels of the instrumental variable, the proportion within the cancer referral network who received SABR with curative intent versus surgery. 6m, six months prior ;COPD, chronic obstructive pulmonary disorder; HFRS, Hospital Frailty Risk Score; SABR, stereotactic ablative radiotherapy.

The IV approach will report comparative effectiveness and cost-effectiveness across the overall eligible study population. The first stage models will estimate the probability of receiving SABR versus surgical resection given baseline covariates and the IV.^72^ The second stage outcome models will use the general linear models framework and choose the specific model according to whether the endpoint is binary (e.g., mortality at 3 years), continuous (e.g., costs) or time-to-event (e.g., time to death). All estimates will be reported with bootstrapped CIs that make appropriate allowance for clustering.

The IV approach will also report comparative effectiveness and cost-effectiveness according to prespecified subgroups including sex; age group; pre-existing cardiovascular disease or not; hospital frailty score (corresponding to fit, low or intermediate risk); Zubrod performance status (0–2), tumour stage, tumour histology and year of diagnosis.

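### Hospital days and costs are outcomes, but the patient's own hospital use before diagnosis, available in the linked records, is not named as a baseline covariate; adding it is a cheap, modest gain in precision

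*Protocol article*

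**What the plan says.** **Outcomes.** Follow-up period and outcomes states: "The number of days in hospital in the 12 months after the start of treatment will be recorded". Table 2 lists this measure and incremental costs as secondary outcomes. Resource use and unit costs adds: "We will combine resource use with unit costs to report total costs per patient over 3 years".

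**Covariates.** Covariates and time zero lists demographic and tumour variables from the registry, and Zubrod performance status, which "will be obtained from the Cancer Outcomes and Services Data". For HES it says "we will define comorbidities from inpatient and outpatient visits that include the following diagnoses in the 5 years before the NSCLC diagnosis", and seven conditions follow. It then adds seasonality, treatment waiting time, surgical volume, cancer alliance and NHS region.

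**Frailty.** This appears elsewhere. Table 1 gives one purpose of HES as "Collect measured confounders (e.g., comorbidities and frailty". The key to Figure 3, the plot of baseline covariate balance across the instrument, has "HFRS, Hospital Frailty Risk Score". The subgroup list under Main analyses (base case) includes "hospital frailty score (corresponding to fit, low or intermediate risk".

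**Use in the models.** Main analyses (base case) says: "The first stage models will estimate the probability of receiving SABR versus surgical resection given baseline covariates and the IV". The alternative analysis is inverse probability weighting with regression adjustment, which the article says assumes that there are no unobserved confounders.

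**The concern.** When an outcome is a count of hospital days or a hospital cost, the same quantity measured before baseline is a natural adjustment variable. The article already draws on five years of HES inpatient and outpatient records, yet what it names from them is a set of diagnoses and, through Table 1, frailty. Earlier bed days, admissions and costs are not named anywhere.

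Three things are at stake, none of them large:

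- **Precision.** An instrumental variable (IV) estimate is less precise than a direct comparison, and days and costs are usually skewed, so explaining part of the residual variance is worthwhile.
- **Confounding in the double-robust analysis.** That analysis depends on how fully baseline health is measured. The Introduction itself says that patients with several long-term conditions are less suitable for surgery. A recorded diagnosis does not by itself separate a stable patient from one admitted repeatedly.
- **The instrument check.** Independence of the instrument can be examined only on observed baseline variables, and prior use would make that check more searching.

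**Working it through.** **1. Is prior use named?** The two sides compare as follows.

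| Item | Where named | Patient's own prior use? |
|---|---|---|
| Demographics, tumour data, performance status | Covariates and time zero | No |
| Seven HES comorbidities, 5-year look-back | Covariates and time zero | No (diagnoses) |
| Seasonality, waiting time, surgical volume, alliance, region | Covariates and time zero | No (timing or care setting) |
| Frailty, Hospital Frailty Risk Score | Table 1, Figure 3 key, subgroups | No (a score, not days, admissions or cost) |
| Label for six months prior | Figure 3 key | Cannot be determined; the figure is not shown |

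The instrument is itself computed over the six months before treatment, so the last label may refer to that.

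**2. Are the data in hand?** Yes. The Data section says that HES covers inpatient and outpatient visits, and Table 1 uses it for both resource use and confounders. Days in hospital and route of admission are already to be derived after treatment. The same derivation can be run on the look-back.

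**3. How much precision?** There is no figure of the plan to reproduce here. Table 4 concerns 3-year mortality only (2,887 to 7,110 required, at least 18,000 expected), and no variance, correlation or precision target is stated for days or costs.

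Inputs:
- N = 18,000, from Sample size calculations.
- r = partial correlation of prior use with the later outcome, given treatment and the other covariates. **Assumption**, range 0.1 to 0.4.

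For one instrument Z and treatment D, with residual outcome variance s²:

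Var(IV estimate) ≈ s² × Var(Z) / [N × Cov(Z, D)²]

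A covariate unrelated to the instrument leaves Var(Z) and Cov(Z, D) unchanged and replaces s² by s² × (1 − r²). So the standard error is multiplied by √(1 − r²), and N patients carry the information of N / (1 − r²).

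| r | 1 − r² | SE multiplier | SE reduction | 18,000 / (1 − r²) |
|---|---|---|---|---|
| 0.1 | 0.99 | 0.995 | 0.5% | 18,182 |
| 0.2 | 0.96 | 0.980 | 2.0% | 18,750 |
| 0.3 | 0.91 | 0.954 | 4.6% | 19,780 |
| 0.4 | 0.84 | 0.917 | 8.3% | 21,429 |

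The article reports that observed baseline variables were balanced across the instrument in the pilot data, which fits the condition that the covariate is unrelated to the instrument. Prior use is not known to have been among the variables checked.

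**The case against.** The strongest reply is that this argues from silence in a condensed article. The covariate section is demonstrably incomplete: it omits the Hospital Frailty Risk Score, which Figure 3 and the subgroups show is in use. Table 1 gives its confounders only as examples, the Figure 3 key has an unresolved label, and a fuller plan may list prior use. This stands to the extent that the point cannot be put as an error or a contradiction. It does not remove the suggestion, because no section names the variable and the data are already linked.

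Two stronger readings are tempting and are not supported.

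- *That a frailty marker is left out of the models.* Frailty is a named measured confounder, the frailty score is in the key to the balance figure and is a subgroup, and performance status and comorbidities are covariates. What prior use would add beyond these is unknown.
- *That a loss equal to thousands of patients has been shown.* At r = 0.4 the arithmetic gives 21,429 − 18,000 = 3,429, but r is assumed, and on the standard-error scale this is about 8%. The formula also ignores clustering. The instrument varies by network and period, and a patient-level covariate need not remove the same share of between-network variance.

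It is also fair that the base case uses an instrument precisely to deal with unmeasured confounding, so the confounding argument bears mainly on the double-robust alternative.

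**Conclusion.** The point holds as a modest, inexpensive improvement to the analyses of hospital days and costs. No section names the patient's own prior hospital use as a covariate, and the linked HES look-back would supply it. If the partial correlation lies between 0.1 and 0.4, the standard error falls by about 0.5% to 8%. This rests on the assumed correlation, on prior use being unrelated to the instrument, and on ignoring clustering. The benefit for confounding is confined mainly to the double-robust analysis. The 3-year mortality sample size and primary conclusion are not affected. Separately, the covariate list should name the frailty score so that it agrees with Table 1 and Figure 3.

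**What to change.** 1. In Covariates and time zero, add prior hospital days (or admissions) and, for the cost-effectiveness analysis, prior hospital cost, all from HES. Measure them over one prespecified window that ends before the diagnostic work-up, so that investigations for the index cancer are not counted as baseline use. The documents do not fix a window, so the study team must choose one and state it.
2. Include these variables in both stages of the IV models and in the double-robust models for hospital days and costs.
3. Show them in the check of covariate balance across levels of the instrument.
4. Add the Hospital Frailty Risk Score to the covariate list.

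The cost is a few variables derived from records already linked, and a few lines of text. The small downside is that the window must be fixed in advance and that the new variables will be skewed and will overlap with each other and with the frailty score. Their functional form should be set beforehand, and one measure per outcome model may be enough.

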#### Treatment strategies

Table 3 shows the SABR regimes considered in this study which follow the Royal College of Radiologists’ guidelines,^6^ practice during the COVID-19 pandemic^41^ and expert inputs from the study’s NSCLC clinical panel. Table 3 also presents the codes used to define surgical resection with curative intent for NSCLC. For both treatment modalities, we will apply a grace period of 30 days before and 6 months after NSCLC diagnosis to account for the prioritisation of diagnosis by pathology as defined by the European Network of Cancer Registries^53^ and to allow for treatment waiting times.

**Table 3 T3:** Overview of the regimens and procedures included within the definition of curative SABR and surgical resection

Treatment definition	Source
54 Gy in 3 fractions over 5–8 days	Clinical Oncology Radiotherapy dose fractionation, Royal College of Radiologists^1^
55 Gy in 5 fractions over 10–14 days	Clinical Oncology Radiotherapy dose fractionation, Royal College of Radiologists^1^
60 Gy in 5 fractions over 10–14 days	Clinical Oncology Radiotherapy dose fractionation, Royal College of Radiologists^2^
60 Gy in 8 fractions over 10–20 days	Clinical Oncology Radiotherapy dose fractionation, Royal College of Radiologists^1^
30–34 Gy in 1 fraction	Faivre-Finn *et al*^3^
60–85 Gy in 5 fractions	Input from clinical panel
50 Gy in 5 fractions	Input from clinical panel
50 Gy in 8 fractions	Input from clinical panel
OPCS-4: E54.3 lobectomy	Input from clinical panel
OPCS-4: E54.4 excision of segment of lung	Input from clinical panel
OPCS-4: E54.5 partial lobectomy of lung NEC	Input from clinical panel

Gy, Gray; NEC, not elsewhere classified; OPCS-4, Office of Population Censuses and Surveys Classification of Interventions and Procedures, version 4; SABR, stereotactic ablative radiotherapy.

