#### Outcomes for the CEA

We will calculate the number of life years from the date of treatment start up to 3 years (base case) and for the maximum observation period available (alternative analyses). The NRDS linked data will be used to identify cancer recurrence and disease progression based on diagnoses and procedures captured in subsequent hospital admissions, registration of new tumours and treatment receipt, including surgery, chemo-oncology, immuno-oncology therapy and radiotherapy using a novel approach developed for bowel cancer.^65^ The IV analysis will compare the adjusted proportions of cancer recurrences, common severe adverse events (eg, pneumonia, respiratory distress syndrome or failure and myocardial infarction)^66^ following SABR versus surgical resection. Pending these results, we will apply appropriate HRQoL estimates from the literature.^59^,^61^ For individuals who died of lung cancer, lower HRQoL will be assigned in the six months prior to death.

We will combine survival time with appropriate HRQoL estimates from the literature and use the ‘area under the curve’ approach^67^ to report quality adjusted life years (QALYs) at 3 years from treatment start. We will calculate the incremental net benefit by valuing the incremental QALYs (difference in mean QALYs for SABR vs surgical resection) with alternative threshold levels for cost per QALY gain, including those specified by NICE (eg, £20 000 and £30 000).

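### As written, the admission-level rule for grade 3-4 adverse events does not count complications during the index surgical stay, so ascertainment differs by arm

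*Protocol article*

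**What the plan says.** Four places in the protocol article bear on this.

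- **Follow-up period and outcomes.** The stated data items, window and purpose are "reasons and route of admission (eg, via emergency room) in the 90 days following the start of treatment to identify admissions attributable to grade three"; the same sentence extends this to grade 4 events after both modalities and refers the reader to the cost-effectiveness section. The unit is the admission, and one rule serves both arms.
- **Covariates and time zero.** Time zero is "the first date that SABR with curative intent is received or surgical resection is undertaken".
- **Outcomes for the CEA.** The IV analysis will compare adjusted proportions with recurrence and with "common severe adverse events (eg, pneumonia, respiratory distress syndrome or failure and myocardial infarction"). No window is given, and nothing says whether diagnoses made during the index surgical stay count. The next step is "Pending these results, we will apply appropriate HRQoL estimates from the literature".
- **Strengths and limitations.** The linked data are said not to capture the toxicity of treatments, and the published literature is to be used for such outcomes in the cost-effectiveness analysis.

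**The concern.** The rule looks the same in both arms but does not see the same things in both arms. A surgical patient enters the observation window in the middle of an admission made for the resection. A serious complication in that stay changes neither the reason for that admission nor its route, and it starts no new admission. A SABR patient has no resection stay, so a serious event of the same kind that needs hospital care would normally appear as a new admission with its own reason and route.

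At stake is the between-arm comparison of severe adverse events, and through it the quality-of-life values used for QALYs and net benefit. Incremental net health benefit is a listed secondary outcome in Table 2. There is also an imbalance within the economic analysis. The Resource use and unit costs section separates critical-care from ward time, so an in-stay complication raises the surgical cost, while on the natural reading of the rule it would not register as an adverse event on the outcome side.

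**Working it through.** The plan gives no adverse event rate or timing, so there is no figure to reproduce. The check is a reading of the sections against each other, followed by simple algebra.

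**1. The same event traced through the rule**

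| | Surgery | SABR |
|---|---|---|
| Time zero | Operation date, inside the index admission | First date SABR is received |
| Severe pneumonia soon after time zero | Arises in the stay already under way | Leads to a new admission if hospital care is needed |
| Reason and route seen by the rule | Those of the resection admission | Those of the pneumonia admission |
| Counted as an admission attributable to an adverse event? | No, on the natural reading | Yes |

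An admission made for a resection is not attributable to a complication that followed the resection.

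**2. Effect on the comparison**

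Let P_R and P_S be the true proportions with a severe event in the window after SABR and after surgery. Let m be the proportion of all surgical patients whose only severe events in the window occurred before discharge from the index stay. Assume that this mechanism misses nothing after SABR.

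- Recorded proportion, surgery: P_S − m
- Recorded proportion, SABR: P_R
- Recorded difference, SABR minus surgery: P_R − (P_S − m) = (P_R − P_S) + m

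Each percentage point of m moves the difference by one point in the direction that makes surgery look safer. The documents give no value for m; the range is 0 ≤ m ≤ P_S.

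**3. Why the IV analysis does not help**

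The instrument deals with confounding of treatment choice. Here the loss of events is a consequence of having surgery. A valid instrument would estimate without bias the effect on the recorded outcome, which still contains m.

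**4. What is not touched**

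- All-cause and lung-cancer mortality do not use this rule, so fatal complications still count as deaths.
- Hospital days over 12 months and costs over 3 years are built from stays and resource use, so they reflect a prolonged index stay.
- Adverse events are not in the Table 2 outcome list.

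**5. Window**

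The 90-day window is 90/365.25 = 24.6% of the 12-month period used for hospital days and 90/(3 × 365.25) = 8.2% of the 3-year horizon of the cost-effectiveness analysis. These are shares of time, not of events. They show only that the window for the cost-effectiveness comparison has to be stated.

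**The case against.** **The index stay is not expressly excluded.** This is the best counter-argument. The sentence does not say that nothing else will be used, it points to the cost-effectiveness section, and that section names event types without tying them to reason, route or 90 days. The Data section says that HES holds diagnoses and procedures for inpatient visits, so the reasons for admission could be meant to include codes recorded during the index episode. The code-level definition may also sit in a fuller document. This stands as a limit: the gap is the natural reading, not a stated exclusion. It does not remove the point, because the only operational rule in print works on admissions attributable to adverse events, and the cost-effectiveness section offers no other rule.

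**Toxicity is already conceded as a limitation.** True, but the concession says the literature will be used, whereas two other sections derive adverse events from the linked data. That adds a contradiction to resolve and does not settle how index-stay events are handled.

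**Stronger readings that the documents do not support:**

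- *The rule misses late SABR toxicity.* The window does end at day 90. The longest course in Table 3, "60 Gy in 8 fractions over 10–20 days", could leave as little as 90 − 20 = 70 days after the last fraction, although other courses leave more. The documents say nothing about when SABR toxicity appears, so no claim about the share missed can rest on them.
- *The event list omits radiation-specific diagnoses.* The list is given as examples, so absence from it is not exclusion.
- *The 90-day window is an error.* Choosing 90 days over 12 months trades completeness against specificity and is a judgement.
- *The bias can be put at some number of percentage points.* That would need in-stay and post-discharge event rates, which are not given.

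**Conclusion.** The point holds in a limited form. As printed, the rule for grade 3-4 adverse events works on admissions and does not provide for complications during the index surgical stay. Severe events would then be under-counted in the surgical arm, and the adverse event comparison would lean towards surgery by m, a quantity the documents do not let anyone estimate. The conclusion assumes that the reason and route of the index admission are those of the resection, and that SABR has no comparable stay in which events are hidden.

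The reach is the IV comparison of severe adverse events and the quality-of-life values chosen after it. Mortality, bed-days and costs are unaffected. The definition should be changed before analysis. If the authors already intend to use index-stay diagnoses, one sentence closes the main part; the window for the cost-effectiveness comparison and the conflict with the stated limitation would still need settling.

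**What to change.** 1. Define severe adverse events from HES diagnosis, procedure and critical-care records in any episode from time zero, and say explicitly that the index surgical admission is included. Use the same event code list in both arms.
2. State the window that applies to the severe adverse event comparison in Outcomes for the CEA.
3. Reconcile Follow-up period and outcomes and Outcomes for the CEA with Strengths and limitations: say which adverse events come from the linked data and which from the literature.
4. Optional: report days 91-365 separately as a sensitivity analysis. The downside is that later admissions are less specific to treatment.

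The cost is protocol and analysis plan wording plus some additional HES coding. HES is already linked, and critical-care time is already to be extracted for costing, so no new data source is needed.
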